**Methods/Designs:**

Our goal is to test the hypothesis that patients with painful osteoporotic vertebral compression fractures who undergo vertebroplasty have less disability and pain at 1 month than patients who undergo a control intervention. The control intervention is placement of local anesthesia near the fracture, without placement of cement. One hundred sixty-six patients with painful osteoporotic vertebral compression fractures will be recruited over 5 years from US and foreign sites performing the vertebroplasty procedure. We will exclude patients with malignant tumor deposit (multiple myeloma), tumor mass or tumor extension into the epidural space at the level of the fracture.

We will randomly assign participants to receive either vertebroplasty or the control intervention.

Subjects will complete a battery of validated, standardized measures of pain, functional disability, and health related quality of life at baseline and at post-randomization time points (days 1, 2, 3, and 14, and months 1, 3, 6, and 12). Both subjects and research interviewers performing the follow-up assessments will be blinded to the randomization assignment. Subjects will have a clinic visit at months 1 and 12. Spine X-rays will be obtained at the end of the study (month 12) to determine subsequent fracture rates. Our co-primary outcomes are the modified Roland score and pain numerical rating scale at 1 month.

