### Baseline assessment

All subjects will complete baseline assessments prior to the randomized treatment assignment. Subjects will provide the study with spine images (either plain film X-ray or MRI) to document the fracture(s). The research coordinator will complete a chart review to obtain pertinent health variables, including height and weight, prior osteoporotic fractures and back procedures, osteoporosis history, current and historical osteoporosis therapy and oral corticosteroid use, and current medication for back pain. Subjects will complete a battery of standardized measures of pain, physical disability and health related quality of life, as well as comorbidities, back pain medications and demographics. A brief physical examination will be performed, including blood pressure and brief neurological assessment (motor system, sensation, reflexes, and straight leg raises).

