The primary economic outcome measure is the EQ-5D preference score [22]. The EQ-5D assesses three levels of severity (no problems, moderate problems, and extreme problems) across each of five dimensions of health (mobility, self-care, usual activities, pain/discomfort, and anxiety/depression). Responses to the EQ-5D can be converted into a weighted health state index using predetermined values derived from general population surveys [22]. This index is anchored at zero (very severe health status equivalent to death) and one (best imaginable health status). By combining this quality of life index with information on patient survival, a quality adjusted life year (QALY) can be calculated.

We will calculate the incremental net benefit (INB) statistic of vertebroplasty, defined as:

INB = λ(Effect_vertebroplasy _- Effect_control_) - (Cost_vertebroplasty _- Cost_control_),

where λ is the amount that society is willing to pay for an average improvement of one quality adjusted life year. Rather than use one arbitrary cut-off (e.g., $100,000 per QALY) to define cost-effectiveness, we will present the results as a cost-effectiveness acceptability curve (CEAC). The CEAC uses non-parametric bootstrap methods [16] to determine, for any given willingness-to-pay cut-off, the probability that vertebroplasty is cost-effective. CEAC curves enable decision-makers with different budget constraints to judge the cost-effectiveness of interventions in their setting.

In the primary analysis, we will exclude subjects with missing cost or effectiveness data. However, as data may not be missing at random, we will conduct a secondary analysis using multiple imputation methods to estimate missing data [23]. We will use univariate and multivariate sensitivity analysis to estimate which non-stochastic parameters (e.g. unit costs, discount rate) have the greatest influence on our findings.

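### The net-benefit analysis names no adjustment for baseline EQ-5D; adding it would sharpen the QALY difference at no cost, though the unadjusted analysis is not invalid

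*Protocol article*

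**What the plan says.** All places are in the Protocol article.

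- **Effect measure** (Analysis, economic part): "The primary economic outcome measure is the EQ-5D preference score". The QALY is described in general terms: "By combining this quality of life index with information on patient survival, a quality adjusted life year (QALY) can be calculated". No area-under-the-curve rule or baseline handling is given.
- **Estimator** (same section): "INB = λ(Effect_vertebroplasy _- Effect_control_) - (Cost_vertebroplasty _- Cost_control", with uncertainty shown by an acceptability curve (CEAC): "The CEAC uses non-parametric bootstrap methods [16] to determine, for any given willingness-to-pay cut-off, the probability that vertebroplasty is cost-effective".
- **Missing data** (same section): the primary economic analysis drops subjects who lack cost or effect data. Multiple imputation is secondary, on the stated ground that data may not be missing at random. The sensitivity analyses vary non-stochastic inputs such as unit costs and the discount rate.
- **Baseline data** (Baseline assessment): "Subjects will complete a battery of standardized measures of pain, physical disability and health related quality of life". The abstract places these measures "at baseline and at post-randomization time points (days 1, 2, 3, and 14, and months 1, 3, 6, and 12", and Measures lists the EQ-5D as a secondary outcome. The article does not say which follow-up contacts include the EQ-5D.
- **Adjustment elsewhere** (Analysis): all analyses are stratified by site. Secondary analyses adjust for baseline characteristics, with pain severity and functional status as examples. A covariate-controlled comparison follows the methods for secondary outcomes, and a covariate-adjusted logistic model is planned for serious adverse events if numbers allow. None of these names baseline EQ-5D or is tied to the INB.

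**The concern.** The economic text is fairly detailed: it gives the formula, the resampling method, the primary data set, the imputation and the sensitivity analyses. Followed as written, it leads to a simple difference between arms. Where the article intends covariate adjustment it says so, and it does not say so here.

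Baseline utility usually predicts later utility. If the arms differ at baseline, part of that difference reappears in the QALY difference and is then multiplied by the willingness-to-pay value. Bootstrapping the observed subjects reflects this as sampling variability but does not centre the estimate on balanced arms. None of the listed sensitivity analyses would reveal it.

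Two features of this trial make it worth settling. The sample is small: the Discussion now expects 100 subjects. And the primary economic analysis uses completers, among whom randomisation no longer guarantees balance. What is at stake is the precision of the INB and where the CEAC sits given the imbalance that actually occurs.

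**Working it through.** **The plan's own figures.** None is given for the economic analysis. The sample-size figures reproduce: for the Roland with 75 per arm, SD 6.7 and two-sided 5% (assumed), power is 95.5% for 4 points and 78.3% for 3, against the stated 95% and 78%. They do not bear on this point.

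**Complete cases at one year.** Inputs: 100 enrolled (Discussion); expected withdrawal of 15% at one month and a further 10% at one year (Data Management).
- Both percentages of those enrolled: 100 × (1 − 0.15 − 0.10) = 75, or 37.5 per arm.
- Second percentage of those remaining: 100 × 0.85 × 0.90 = 76.5, or 38.25 per arm.

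I use 38.

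**Assumptions, none in the documents.** EQ-5D SD 0.25 at every time; QALY as a trapezoid area under the curve at months 0, 1, 3, 6 and 12. Two correlation patterns are used: (a) baseline with each follow-up 0.2 to 0.5, and follow-ups with each other 0.6; (b) one equal correlation of 0.3 to 0.7 between all times.

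**Formulas.**
- Trapezoid weights w: 0.0417 (baseline), 0.125, 0.2083, 0.375, 0.25.
- Slope of QALY on baseline: b = 0.0417 + ρ × 0.9583, where ρ is the correlation of baseline with follow-up.
- Squared correlation of baseline with QALY: r² = b² / (w′Rw), with R the correlation matrix. Adjustment removes a fraction r² of the variance of the QALY difference.
- One-standard-error baseline imbalance: 0.25 × √(2/38) = 0.0574.
- Shift in the QALY difference = b × 0.0574.

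| Pattern | b | r | Variance cut r² | Shift (QALY) | At $100,000/QALY |
|---|---|---|---|---|---|
| (a) ρ = 0.2 | 0.233 | 0.284 | 8% | 0.013 | about $1,300 |
| (a) ρ = 0.3 | 0.329 | 0.399 | 16% | 0.019 | about $1,900 |
| (a) ρ = 0.5 | 0.521 | 0.624 | 39% | 0.030 | about $3,000 |
| (b) ρ = 0.3 | 0.329 | 0.473 | 22% | 0.019 | about $1,900 |
| (b) ρ = 0.5 | 0.521 | 0.655 | 43% | 0.030 | about $3,000 |
| (b) ρ = 0.7 | 0.712 | 0.807 | 65% | 0.041 | about $4,100 |

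Worked line, (b) ρ = 0.5: the sum of squared weights is 0.2639, so w′Rw = 0.5 + 0.5 × 0.2639 = 0.632; r² = 0.521² / 0.632 = 0.43; shift = 0.521 × 0.0574 = 0.030.

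**Sensitivity.** The shift is proportional to the SD: at 0.20 the range is 0.011 to 0.033, and at 0.30 it is 0.016 to 0.049. The variance cut does not depend on the SD. The dollar scale uses the article's illustrative value ("Rather than use one arbitrary cut-off (e.g., $100,000 per QALY) to define cost-effectiveness").

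**Route of the carry-over.** The direct part, through the baseline point of the curve, is 0.0417 × 0.0574 = 0.0024 QALY, or about $240. If the EQ-5D were taken at every listed contact, including days 1, 2, 3 and 14, the baseline weight would be 0.0014 and the direct part about $8. Nearly all of the shift comes through correlation with follow-up scores.

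**From QALY to INB.** Var(INB) = λ²Var(ΔQALY) + Var(ΔCost) − 2λCov(ΔQALY, ΔCost). The table shows the reduction in the first variance only. The documents give no cost variance or covariance, so the reduction for the INB cannot be computed.

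**The case against.** The strongest reply is that this treats silence as a choice. The article never calls the effect difference raw or unadjusted; the formula is a definition that an adjusted difference also satisfies, and a bootstrap can be run on either. This is a condensed article, and an analysis plan not shown may settle the matter. That stands, so the point is worded as an adjustment not named, and its absence is not called an error. It remains worth raising because this section does lay out the estimator step by step and, followed literally, yields the less precise version.

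Four stronger readings are tempting and not supported:

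- **That the planned analysis is biased or its CEAC invalid.** Over randomisation the unadjusted difference is unbiased, and the bootstrap spread already includes baseline variation. In the table the shift equals r standard errors of the QALY difference, about 0.28 to 0.81. Chance can move a CEAC across 50% under any valid estimator. The reassurance is weaker for completers, but adjustment helps there only with the part of dropout related to baseline EQ-5D.
- **That baseline counts heavily as the first point of the QALY.** Its weight is at most about 0.042 on the schedules considered.
- **That the variance cut is a gain in power for the economic conclusion.** It concerns the QALY difference. The planned output is an acceptability curve, with no significance threshold, and cost variance also enters.
- **That site is ignored.** The article already stratifies all analyses by site.

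It is also fair that the covariate-controlled comparison in Analysis follows the secondary outcomes, among them the EQ-5D. But it neither names the baseline score nor reaches the INB.

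**Conclusion.** The point holds as an improvement in precision. The economic analysis, as described, leaves out a baseline predictor that the trial appears to collect, in a setting of roughly 37 to 38 complete cases per arm. A one-standard-error imbalance would move the QALY difference by about 0.013 to 0.041, and adjustment would remove about 8% to 65% of its variance. The width of those ranges reflects how little the documents say: SD, correlations, EQ-5D schedule and QALY rule are all assumed, and the upper end needs an equal correlation of 0.7 from baseline through month 12. Direction is secure wherever baseline and follow-up utility are positively correlated; size is not. No statement in the article is shown to be wrong.

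**What to change.** In the economic part of Analysis, state that:

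1. incremental QALYs are estimated by regression on treatment, baseline EQ-5D and site, and incremental costs by regression on treatment and site (the site terms carry out the stratification already promised);
2. the INB is formed from these two adjusted differences;
3. for the CEAC, subjects are resampled within arm, each subject's cost and effect stay paired, and both regressions are refitted in every bootstrap sample;
4. the unadjusted INB is reported as a sensitivity analysis.

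Fixing this before the data are seen also removes any later choice between two curves. The cost is wording and a little programming. On the article's account of the baseline battery, no new data, visits or subjects are needed; the sponsor should confirm that the EQ-5D is part of it.

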For primary analyses, an "intention-to-treat" strategy will be employed, such that each subject is analyzed in the group to which he or she is randomized, regardless of actual compliance with the intended intervention. This strategy requires minimal assumptions and maintains the random allocation, although intervention effects may be "diluted" if cross over between procedures is high. We will stratify all analyses for site. Non-adherence and/or dropout complicate analysis of follow-up data. Consideration of missing data is essential to characterize the potential for selection bias through attrition. When appropriate, missing follow-up data for subjects who withdraw will be imputed.

The primary outcomes of Roland and pain measure will be assessed at the one-month time point. This allows adequate time for any intervention benefit to manifest, and is the final assessment prior to the opportunity to select further treatment (crossover). The primary analysis will test for the efficacy of vertebroplasty using a permutation test based on the randomization distribution. Such analysis allows formal inference relying solely on the random assignment of subjects for validity (i.e., makes no additional statistical assumptions). Confidence intervals for the magnitude of treatment effect will be obtained using linear regression with a treatment indicator as the predictor of interest and using dummy variables to stratify on site. We will perform a similar analysis using the 0–10 numerical pain rating scale at one month. Secondary analyses will describe the complete time profile for the Roland and the pain ratings through one year using methods appropriate for the analysis of repeated measures [16].

In addition to hypothesis tests based on the randomization scheme, we will conduct secondary analyses that adjust for important baseline characteristics, such as baseline pain severity, and functional status. We will conduct limited exploratory analyses to assess evidence for differential treatment response by subject subgroups by testing treatment-covariate interactions for factors that are specified *a priori *in a detailed analysis plan to be created prior to data analysis. We will also perform a subgroup analysis examining whether enrolling early or late in the study had an effect on outcome. This will help determine if a significant learning curve was present and, if so, the magnitude of the effect.

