### Data Management

Data acquisition, handling, and storage are under the direction of the senior programmer of the Data Coordinating Center at the University of Washington. An HTML form-based web application is in use for conducting subject assessments as an efficient method for managing data for this multi-center, national trial. Data will be housed in a secure, centralized database at the University of Washington. The system will automatically perform edit and logic checks to validate the data for quality and completeness as they are being entered. A quality control audit will be performed on a monthly basis and the results printed in an interim report. Staff at the data-coordinating center will monitor the compliance of each study hospital with the study procedures and data quality.

We will document the number and proportion of subjects eligible for and compliant with each follow-up. Careful efforts will be made to minimize missing data, though some will inevitably occur. Subjects who withdraw from the study will be tabulated with the reasons for the withdrawal. Subjects who die during the study (unrelated to study or procedure) will be tabulated also. If the proportion of subjects withdrawn is larger than the expected 15% at one month and additional 10% at one year from either arm, an analysis of the demographic and prognostic characteristics will be made between subjects who withdraw and those who remain in the study. For continuous variables, parametric or non-parametric analysis of variance will be used. For categorical variables, Chi-square or Fisher's exact test will be applied.

When individual items are missing from a scale, we will calculate the percent of missing items. If the missing items are less than 10%, we will impute values using the mean of the remaining items. If more than 10%, the scale score will be missing, and unavailable for analysis at that time point.

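### The economic plan gives possible non-random missingness as its reason for multiple imputation, which as usually run assumes missing at random, and the article describes no analysis that varies that assumption

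*Protocol article*

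**What the plan says.** All of this is in the protocol article.

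- **Analysis, primary economic set:** "In the primary analysis, we will exclude subjects with missing cost or effectiveness data".
- **Analysis, next sentence, opening with a contrasting *However*:** "as data may not be missing at random, we will conduct a secondary analysis using multiple imputation methods to estimate missing data". A reference is cited for the method. No imputation model, shift, pattern-mixture model or selection model is named.
- **Analysis, economic sensitivity analysis:** its purpose is limited to finding the influential fixed inputs, a "sensitivity analysis to estimate which non-stochastic parameters (e.g. unit costs, discount rate) have the greatest influence on our findings".
- **Analysis, clinical follow-up:** "When appropriate, missing follow-up data for subjects who withdraw will be imputed". No method or assumption is attached. The same paragraph calls attention to missing data essential for judging selection bias from attrition.
- **Data Management:** if withdrawal is "larger than the expected 15% at one month and additional 10% at one year from either arm", then "an analysis of the demographic and prognostic characteristics will be made between subjects who withdraw and those who remain in the study".

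**The concern.** The plan names a threat and offers a method as the response to it. Read literally, the threat is that a subject's cost or EQ-5D value is missing for reasons tied to the value itself. Multiple imputation in its usual form fills in values from the relation seen among observed subjects, so it takes that threat to be absent once the imputation variables are accounted for.

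What is at stake is how the two planned results would be read together. If the complete-case and imputed results agree, the stated rationale invites the conclusion that non-random missingness has been checked. Neither analysis examines it. If subjects doing badly leave more often, and more so in one arm, the incremental net benefit and the acceptability curve can both be displaced with no planned result to show it.

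**Working it through.** The plan states no figure on this point, so there is none to reproduce.

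**1. Which described provision varies the missing-data assumption?**

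| Provision | Varies the assumption? |
|---|---|
| Complete-case primary analysis | No; it drops incomplete subjects |
| Multiple imputation, secondary | Not as usually run; assumes missing at random given the model |
| Economic sensitivity analysis | No; limited to inputs such as unit costs and discount rate |
| Imputation of clinical follow-up | No assumption stated |
| Leavers compared with stayers | No; uses observed characteristics, and only above a withdrawal threshold |

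**2. Does usual multiple imputation repair the problem?** An illustrative simulation used 25% missing per arm, which follows the Data Management figures (15% + 10%). Everything else was assumed: SD 0.20, correlation with baseline 0.5, true EQ-5D difference 0.050, selective missingness in the control arm only, and 20 imputations by normal regression on baseline within arm.

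| Missingness | Complete case | Multiple imputation |
|---|---|---|
| Completely at random | 0.050 | 0.050 |
| Depends on baseline | 0.028 | 0.049 |
| Depends on the unseen score | 0.007 | 0.017 |

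Imputation almost fully repairs the second case. In the third, the bias falls only from 0.050 − 0.007 = 0.043 to 0.050 − 0.017 = 0.033.

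**3. Scale in QALYs and net benefit.** With a departure in one arm only:

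shift = share missing × EQ-5D departure × share of year affected, summed over groups of leavers.

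Inputs:
- Share missing, high: 15% + 10% = 25% (Data Management; 1 − 0.85 × 0.90 = 23.5% if compounded).
- Share missing, low: 1 − 0.90 × 0.90 = 19% (90% one-month follow-up from Sample Size, then a further 10%; 20% if added).
- Departure from the missing-at-random prediction: 0.05 to 0.15, assumed.
- Share of year: half for all, at the low end (assumed). At the high end, 11/12 for those gone by month one and 11/24 on average for later leavers, assumed evenly spread over months 1 to 12.
- Willingness to pay: $100,000 per QALY, the article's own example.

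Results:
- Low: 0.19 × 0.05 × 0.5 = 0.00475, about $475 per subject. With the even-spread rule instead, 0.10 × 0.05 × 11/12 + 0.09 × 0.05 × 11/24 = 0.0066, about $665.
- High: 0.15 × 0.15 × 11/12 + 0.10 × 0.15 × 11/24 = 0.0206 + 0.0069 = 0.0275, about $2,750 per subject.
- Same departure and same share missing in both arms: the two shifts subtract to zero.

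**4. Against sampling error.** With 100 enrolled (Discussion), 50 per arm, 25% missing and the assumed SD of 0.20, there are 37.5 complete cases per arm. The standard error of a difference in EQ-5D score is 0.20 × √(2/37.5) = 0.046.

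**The case against.** The sentence at issue follows directly on the exclusion of incomplete subjects and is set against it. In that context the authors' worry is about complete-case analysis, and their phrase may be loose wording for not missing *completely* at random. Multiple imputation is then the natural next step, and the simulation supports it: where missingness depends on baseline, it restores nearly the whole difference. This reading is plausible. It reduces the fault to the wording, but the wording still needs correcting, because as it stands it claims more for the imputation than the usual method delivers.

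A reader might go further and infer that the trial never tests non-random missingness. The documents do not support that. The article is condensed, it cites a source for its imputation methods that is not at hand, and imputation can be run under not-at-random models. A fuller plan may do so. What can be said is that this article describes no such analysis.

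A reader might also apply 11/12 of a year to all 25% missing and get 0.25 × 0.15 × 11/12 = 0.034 QALY. That overstates the top end. Ten of the 25 points are withdrawals after month one, and assessments are scheduled at months 3 and 6, so later leavers contribute data first.

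It is also fair that the departures, their confinement to one arm and the SD are assumptions, and that the resulting shifts lie below one standard error as computed above. The article also states no rule that agreement between the two analyses means robustness. These points limit the importance of the concern. They do not remove it, since a bias of this kind is not reflected in the bootstrap behind the acceptability curve.

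**Conclusion.** The point holds in limited form. The article pairs a literal concern about non-random missingness with a method that usually assumes missing at random, and describes nothing that varies that assumption. Under either reading of the phrase, agreement between the two planned analyses would be silent about missingness that depends on unseen values.

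The illustrative size is 0.005 to 0.028 QALY, about $475 to $2,750 per subject at $100,000 per QALY. It rests on the assumed one-arm departures and timing of withdrawal, and would be zero if both arms were affected alike. No comparable figure for costs can be derived from the article. The point is minor: it concerns only the economic evaluation, not the one-month Roland and pain comparison.

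**What to change.** Describe the multiple-imputation analysis as the missing-at-random analysis. If the intended worry was only that complete cases may be unrepresentative, change the rationale to say that data may not be missing *completely* at random.

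In addition, prespecify a delta-adjusted (pattern-mixture) version. Shift the imputed EQ-5D values and the imputed costs over a stated range, in each arm alone and in both together. EQ-5D reductions of 0.05, 0.10 and 0.15 would match the illustration here, but the range, and a corresponding one for costs, should be the authors' own and be justified. Report the effect on the incremental net benefit and on the acceptability curve.

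The cost is a few further runs of the planned imputation and bootstrap, with no new data and no design change. The downside is a wider range of reported results. Making multiple imputation the primary analysis would not substitute for this, because the same assumption would remain untested.

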## Methods/Design

### Participants and Setting

INVEST (INvestigational Vertebroplasty Efficacy and Safety Trial) is a multi-center, randomized, controlled trial comparing percutaneous vertebroplasty to a control intervention for patients with painful osteoporotic vertebral compression fractures refractory to medical therapy. The control intervention involves injection of a long-acting, local anesthetic agent adjacent to but not within the vertebral body, and no injection of cement. Subjects will be recruited from patients scheduled for vertebroplasty evaluations at participating US and foreign INVEST clinical sites. Each INVEST site will be approved by their local Institutional Review Board (IRB). Patients meeting the inclusion criteria may enroll in the study following an informed consent process.

Subjects must have a recent, painful vertebral compression fracture at levels T4 to L5 confirmed with a physical examination and radiographic imaging. The fracture must have occurred within the previous 12 months, they must have tried medical therapy for pain and have a current subjective pain rating of at least 3 on a 0 – 10 scale. Subjects are required to have a confirmed diagnosis of osteoporosis or osteopenia. Patients are excluded if they have malignant tumor deposit (multiple myeloma), tumor mass or tumor extension into the epidural space at the level of the fracture, malignancy, pedicle fracture, or cord compression. Other eligibility criteria are: at least 50 years old, no recent surgery (within 60 days), access to a telephone, no local or systemic infection, no concomitant hip fracture, no contraindications to conscious sedation, speaks English well enough to answer all health questions, not pregnant, and no evidence of dementia (able to give informed consent).

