The serious adverse event (SAE) complication rates occurring within one month of surgery for the device-treated and control subjects will be evaluated descriptively in aggregate and separately. The SAE rate for each group will be estimated and the corresponding 95% exact binomial confidence intervals will be computed. If the number of events is sufficiently large to allow more sophisticated analysis, the rates between the vertebroplasty and control subjects will be compared by logistic regression with covariate adjustment. The data will be presented by total numbers of events and by total numbers of subjects with at least one event. The complication rates including subsequent fractures will be descriptively analyzed through two years post-treatment. The rates and the corresponding 95% exact confidence intervals will be computed.

Based on 12-month plain radiographs, as compared to baseline radiographs, we will compare the proportion of subjects in the two study arms suffering at least one new-onset fracture using the binomial test. We will use the Student t-test to compare the two groups in terms of the mean number of new fractures and the mean number of vertebral levels between the treated levels and new fracture levels.

Non-serious adverse events will be tabulated individually and overall through one year post treatment. The rates will be estimated for the device-treated and control subjects separately and the exact binomial 95% confidence limits will be calculated.

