### Safety Monitoring

If at any time after the procedure (vertebroplasty or control) is performed there are any changes in physical health, the event(s) will be reported to the appropriate authorities (DSMB, NIH, and all site PIs and IRBs) as soon as it is known and will be followed until resolution.

An external six-member Data Safety Monitoring Board (DSMB) is monitoring the study in accordance with NIAMS guidelines. The DSMB determined appropriate stopping criteria and will review the data after 73 and 90 subjects have one-month Roland and pain outcomes for evidence of treatment efficacy or unusual rates of adverse outcomes. KIA Research, Inc. manages the safety monitoring for NIAMS, and serious adverse events will be reported directly to NIAMS and KIA Research, Inc., who will distribute this information to the DSMB chair and safety officer, as they occur. Subsequent vertebral fractures (adjacent and non-adjacent) will be a reportable event, not an adverse event. The principal investigator will notify each site IRB of any death regardless of where the death occurred.

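### The between-arm comparison of one-month serious adverse events is made only if enough events occur, and only by adjusted logistic regression, so sparse events get no planned interval or test for the difference

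*Protocol article*

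**What the plan says.** The protocol article's Analysis section handles SAEs in steps.

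- SAEs "occurring within one month of surgery for the device-treated and control subjects will be evaluated descriptively in aggregate and separately".
- Each arm then gets its own estimate: "The SAE rate for each group will be estimated and the corresponding 95% exact binomial confidence intervals will be computed". Results are shown both as event counts and as subjects with at least one event.
- The arms are contrasted only under a condition: "If the number of events is sufficiently large to allow more sophisticated analysis, the rates between the vertebroplasty and control subjects will be compared". The method is fixed: the rates "will be compared by logistic regression with covariate adjustment". No threshold and no alternative method is given.

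Two other safety outcomes in the same section are useful for comparison. New fractures on 12-month radiographs carry no event-count condition: "we will compare the proportion of subjects in the two study arms suffering at least one new-onset fracture using the binomial test". Non-serious events are reported by arm only: "The rates will be estimated for the device-treated and control subjects separately and the exact binomial 95% confidence limits will be calculated".

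The Safety Monitoring section adds data safety monitoring board reviews after 73 and 90 subjects "for evidence of treatment efficacy or unusual rates of adverse outcomes". Safety is part of the trial's name: "INVEST (INvestigational Vertebroplasty Efficacy and Safety Trial".

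**The concern.** An analysis rule should not let the outcome decide whether the randomised groups are compared. Here the observed SAE count decides it, and the contrast disappears when events are rare. In a trial of this size, rare events are a realistic prospect.

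The single named method adds to the problem. A covariate-adjusted logistic model needs a fair number of events, and ordinary maximum likelihood gives no finite odds ratio when one arm has none. A risk difference with a score or exact interval has neither limitation and can be computed for any count, including zero.

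At stake is the final report. An excess of SAEs in one arm could be visible in two separate rates, yet the plan would supply no interval and no test for the difference between them.

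**Working it through.** **Inputs from the article.** The anticipated total is 100 in the Discussion; 166 stands in the Abstract and in Sample Size. Randomization is blocked to keep the arms balanced, so I take 50 or 83 per arm.

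**Assumed.** The article gives no SAE rate and no trigger. I show risks of 2% to 15%. I use a trigger of 10 subjects with an SAE, and a stricter one of 20 (ten per parameter for treatment plus one covariate). Both triggers are conventions, not the article's.

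**The article's own figures.** None concern SAEs. Its power figures for 100 enrolled (45 per arm after 90% follow-up) reproduce with power = Φ(d / (SD·√(2/n)) − 1.96):

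- Roland: 4 / (6.7·√(2/45)) = 2.832; Φ(0.872) = 80.8%, stated 80%.
- Pain: 1.75 / (2.7·√(2/45)) = 3.074; Φ(1.114) = 86.8%, stated 87%.

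This supports equal arms of about 50 as the current design.

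**How often a trigger would be met.** With equal risk p in both arms, the total number of subjects with an SAE is Binomial(N, p).

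| Risk p | Expected, N=100 | P(≥10), N=100 | P(≥20), N=100 | P(≥10), N=166 |
|---|---|---|---|---|
| 2% | 2 | <0.1% | about 0 | 0.2% |
| 5% | 5 | 2.8% | about 0 | 32% |
| 10% | 10 | 55% | 0.2% | 97% |
| 15% | 15 | 94% | 11% | >99.9% |

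**How often an arm has no events.** The chance that at least one arm is empty is a + b − ab, with a = (1−p₁)^50 and b = (1−p₀)^50.

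- 2% in both arms: 60%.
- 5% in both arms: 15%.
- 10% versus 2%: 0.005 + 0.364 − 0.002 = 37%.

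**Illustration: 6/50 versus 0/50.**

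- Guaranteed output under the plan: 12% (exact 95% CI 4.5 to 24.3) and 0% (0 to 7.1).
- Wilson limits: 5.6% to 23.8% and 0 to 7.1%.
- Newcombe lower limit: 12 − √((12−5.6)² + 7.1²) = 2.4 points.
- Newcombe upper limit: 12 + √((23.8−12)² + 0²) = 23.8 points.
- Fisher's exact two-sided p = 2·C(50,6)/C(100,6) = 0.027.

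Six events fall below either trigger, and one arm is empty, so the named regression would probably not be run and would give no finite odds ratio if it were.

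**What the unconditional estimate would look like with fewer events.** 2/50 versus 0/50 gives 4.0 points (−3.7 to 13.5); 5/50 versus 1/50 gives 8.0 points (−2.2 to 19.5). Both can be computed, and both are imprecise.

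**The case against.** Several objections have force.

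- **Scope.** A reader might infer that the trial's whole safety question goes without a between-arm comparison. The article does not support that: new fractures are compared with no condition, and the monitoring board reviews adverse outcomes. Board review is monitoring, though, and not a final estimate.
- **Information.** A reader might infer that an SAE difference would be hidden. It would not. Counts and rates per arm are always reported, so anyone can derive a difference. What is missing is a planned interval or test for it.
- **Interval overlap.** A reader might infer that harm is to be judged by whether the two separate intervals overlap. The article never proposes this; it calls the analysis descriptive. The weakness of an overlap rule is therefore no evidence against this plan.
- **Frequency.** That the comparison would usually be skipped cannot be derived from the article. The table shows how far it depends on the assumed risk, the assumed trigger and which total is used.
- **The unseen analysis plan.** A full plan could define the threshold, covariates and a fallback, so a missing threshold alone is no finding. What remains is the rule as written, which makes the contrast conditional; a plan that merely filled in the threshold would keep that feature.
- **Small gain.** Descriptive reporting of rare SAEs is a defensible choice in a trial powered for Roland and pain, and limiting the regression to adequate counts is sensible in itself. By enumeration at 50 per arm, with true risks of 5% versus 2%, Fisher's test detects the excess in 1.5% of trials and a Newcombe interval excludes zero in 4%. At 10% versus 2% the figures are 19% and 30%. The case for the change is an honest interval, not power.

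**Conclusion.** The point holds in a limited form. The planned between-arm contrast for one-month SAEs depends on the observed event count and on a model unsuited to sparse data, so the rule drops the contrast when events are few. The fracture comparison in the same section shows that an unconditional contrast was considered feasible for another safety outcome.

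At 100 enrolled and a 10-event trigger, the comparison would probably be skipped if SAE risk is about 5% or less (at most a 2.8% chance of being made). At 10% it is close to even (55%), and at 15% it would nearly always be made (94%). A 20-event trigger would make it unlikely even at 15% (11%). With 166 enrolled, a 10-event trigger would be met in 32% of trials at 5% risk and 97% at 10%. All of this rests on assumed SAE risks and triggers.

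Severity is modest: the raw figures are always available, and only the planned contrast and its uncertainty are at risk.

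**What to change.** - Remove the event-count condition. Always report the risk difference (vertebroplasty minus control) in the proportion of subjects with at least one SAE within one month, with a 95% score or exact unconditional interval.
- Optionally add an exact test stratified by site, in line with the Analysis section's intention to stratify its analyses for site.
- Keep the per-arm rates and exact intervals as description.
- Keep covariate-adjusted logistic regression as a supplementary analysis if events allow.

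The cost is one sentence in the plan and one extra line in the safety table, with no new data. The interval will be wide; the report should call it imprecise and should not read an interval that includes zero as evidence of equal safety.
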